### 3.6. Follow-Up Assessments

The study protocol includes a total of 10 visits, encompassing both baseline assessments and follow-up evaluations. Table 2 outlines the schedule of follow-up visits along with the corresponding testing procedures for the study.

**Table 2 nutrients-16-04297-t002:** Schedule of visits and testing procedures at the CPC-RPA clinic.

		Phase 1				Phase 2				
Visit	1	2	3	4	5	6	7	8	9	10
	Screening Evaluation	Baseline Assessment 1	Start of Fasting and Exercise	End of Fasting 1	End of Refeeding 1	Baseline Assessment 2	Start of Fasting and Exercise 2	End of Fasting 2	End of Refeeding 2	Follow Up Assessment
Visit duration	3 h	2 h	3.5 h	2 h	2.5 h	2 h	3.5 h	2 h	2.5 h	4 h
Consent	☒									
Full body examination (BP, weight, waist/hip cm, vital signs)	☒	☒	☒	☒	☒	☒	☒	☒	☒	☒
Medical history	☒					☒				
Psychosocial questionnaires		☒		☒		☒		☒		☒
Inclusion/Exclusion		☒								
Randomisation			☒							
Fitbit wearable	☒	☒	☒	☒	☒	☒	☒	☒	☒	☒
Food diary		☒	☒	☒	☒	☒	☒	☒	☒	
Urine and faeces sample		☒		☒	☒	☒		☒	☒	☒
Exercise test/intervention	☒		☒				☒			
Fasting blood sample	☒		☒	☒	☒		☒	☒	☒	☒
Capillary glucose and ketones	☒	☒	☒	☒	☒	☒	☒	☒	☒	☒
CGM		☒				☒				
OGTT	☒									☒
DXA		☒								☒
Bodpod		☒	☒	☒	☒	☒	☒	☒	☒	☒
FMD			☒	☒	☒		☒	☒	☒	☒
Autonomic function (ECG)		☒		☒	☒	☒		☒	☒	☒
Buccal mucosa brush sample		☒	☒		☒		☒		☒	☒
Wellbeing/symptoms questionnaire		☒	☒	☒	☒	☒	☒	☒	☒	☒
Adverse Event Assessment	☒	☒	☒	☒	☒	☒	☒	☒	☒	☒

Legend: BP, blood pressure; CGM, continuous glucose monitor, DXA, dual-energy X-ray absorptiometry; ECG, electrocardiogram; FMD, flow-mediated dilation; OGTT, oral glucose tolerance test.

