### 3.4. Baseline Visit

Consenting participants will be enrolled in the trial and undergo baseline clinical assessments, as outlined in Table 1 and Table 2. Following an overnight fast, participants will be screened by collecting medical, dietary, supplementation, and exercise history information and performing the Adult Pre-Exercise Screening System (APSS, 2019, version 2.0) assessment. Baseline evaluations will include the anthropometric measurements; collection of blood, urine, and stool samples; a buccal mucosa swab; an incremental VO_2_peak test on a cycle ergometer; and the completion of a wellbeing and symptoms questionnaire. Research volunteers will also receive instructions from a registered dietitian and study personnel for collecting a 10-day weighed food diary and adhering to fasting protocols. Continuous glucose monitor (CGM) along with a Fitbit device to monitor physical activity and sleep quality and duration will be also set up at baseline assessment.

**Table 1 nutrients-16-04297-t001:** Summary of the visit schedule.

Study Phase	Visit	Visit Title	Approximate Duration of the Visit	Notes
Screening	1	Screening evaluation	3 h	Medical history, blood sample, VO_2_peak test
Phase 1	2	Baseline assessment 1	2 h	Clinical measurements
	3	Start of fasting and cycling exercise/rest period	3.5 h	Fasting starts a night before
	4	End of fasting 1	2 h	Refeeding starts after this visit
	5	End of refeeding 1	2.5 h	4 days after of end of fasting visit
Phase 2	6	Baseline assessment 2	2 h	4 weeks after visit 4
	7	Start of fasting and cycling exercise/rest period	3.5 h	Fasting starts a night before
	8	End of fasting 2	2 h	Refeeding starts after this visit
	9	End of refeeding 2	2.5 h	4 days after of end of fasting visit
	10	Follow up assessment	4 h	4 weeks after visit 8

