A week prior to the fasting intervention, participants will transition to consuming only water for hydration to reduce dependence on caffeine and caloric beverages. They will refrain from strenuous exercise for 48 h before the fasting assessment. On the day before fasting begins, participants will consume only water from 9 PM onward and record all food and drink intake in a diary for submission after the refeeding assessments. During fasting, participants are advised to drink 2–3 litres of water daily, with unflavoured carbonated and mineral water permitted. If participants find it too challenging to continue water-only fasting, they will be provided with 250 mL of vegetable broth sourced from Undivided Food Co., Sydney, Australia, which contains 110 kJ of energy, 0.8 g of protein, 0 g of fat, 5.8 g of carbohydrate and 375 mg of sodium per 250 mL serving. A maximum of two servings per day will be provided. Light physical activities such as walking, yoga, or stretching are encouraged, while strenuous exercise is not recommended. On the last fasting day, following clinic assessments, food will be gradually reintroduced, starting with vegetable broth and transitioning to a low-carbohydrate vegetarian diet. This initial diet will consist of small portions of non-starchy vegetables, salads, and soups for the first day, then gradually transitioning to their normal diet by the end of the refeeding period. This gradual reintroduction of food aims to minimise potential adverse effects and gastrointestinal symptoms. The vegetable broth will be offered upon completion of the fasting visit, along with instructions for the subsequent four days of the refeeding period. The rest of the meals of the refeeding period will not be provided; however, the participants will log all the food and drink into the food diary. Once the refeeding period concludes, participants will be instructed to resume their usual lifestyle for a 4-week washout period.

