### 5.2. Secondary Outcomes

Secondary outcomes to be assessed include:Body weight, waist circumference, and body composition measured by DXA and Bod Pod;Autonomic function, including heart age and heart rate variability, assessed through resting electrocardiography;Blood pressure;Endothelial function evaluated by flow-mediated vasodilation;Continuous monitoring of blood glucose kinetics;Capillary ketones and glucose levels using a portable test strip-based meter;Oral glucose tolerance test to assess glucose tolerance and insulin action;Serum fasting free fatty acids, BHB, acetoacetate, BHB-to-acetoacetate ratio, and lipid profile;Serum concentration of insulin, IGF-1, IGFBP-1, IGFBP-2, IGFBP-3, FGF21, cortisol, testosterone, estradiol, sex hormone-binding globulin (SHGB), T3, Klotho, BDNF, and Beta-Amyloids (Aβ40 and Aβ42);Markers of inflammation, including high-sensitivity C-reactive protein, cytokines (IL-6, TNF-alpha), and chemokines (MCP1);Markers of oxidative stress, including urinary F-2 isoprostanes and 8-hydroxy-2′-deoxy Guanosine.

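### The only pre-fast resting ECG is at visits 2 and 6, at an unstated interval before the fast, so the before-after change in heart rate variability may include part or all of the pre-fast run-in

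*Protocol article*

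**What the plan says.** HRV is a secondary outcome. Section 5.2 lists "Autonomic function, including heart age and heart rate variability, assessed through resting electrocardiography", and the aims in section 2 name change in HRV among the secondary objectives.

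Table 2 in section 3.6 fixes when it is measured. The row beginning "Autonomic function (ECG" is ticked at visits 2, 4, 5, 6, 8, 9 and 10. The FMD row is ticked at visits 3, 4, 5, 7, 8, 9 and 10. The row "Fasting blood sample" is ticked at visits 1, 3, 4, 5, 7, 8, 9 and 10.

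Section 4.1 sets two conditions before each fast:

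- Drinks: "A week prior to the fasting intervention, participants will transition to consuming only water for hydration to reduce dependence on caffeine and caloric beverages".
- Exercise: "They will refrain from strenuous exercise for 48 h before the fasting assessment".

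Between the phases, once refeeding is over, "participants will be instructed to resume their usual lifestyle for a 4-week washout period". Table 1 places visit 6 only as "4 weeks after visit 4". The article does not give the interval from visit 2 to visit 3 or from visit 6 to visit 7.

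**The concern.** A before-after change is attributable to the fast only if the baseline is taken under the conditions that hold when the fast begins. FMD and fasting blood meet this, because their baselines are at visits 3 and 7, after the water-only week and the 48 h without strenuous exercise. The ECG baseline is earlier. Whatever part of the run-in falls between visit 2 and visit 3, or between visit 6 and visit 7, is counted in the HRV change together with the fast.

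If the run-in itself moves resting HRV, the shift enters both periods in the same direction. Averaging over participants or periods would not remove it, and no non-fasting arm is available from which to estimate it. A statement about what a three-day fast does to HRV or heart age would then partly describe stopping caffeine and resting.

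**Working it through.** The plan has no figure of its own to reproduce here. The check is a comparison of the schedule rows, day arithmetic on the stated intervals, and an illustration of size under stated assumptions.

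**1. Last measurement before each fast (Table 2)**

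| Measure | Phase 1 | Phase 2 |
|---|---|---|
| Resting ECG (HRV, heart age) | visit 2 | visit 6 |
| FMD | visit 3 | visit 7 |
| Fasting blood | visit 3 | visit 7 |

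The ECG is not the only measure placed this way. Urine and faeces samples and the psychosocial questionnaires also have their last pre-fast measure at visits 2 and 6.

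**2. How much of the run-in falls inside the HRV change**

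Let g be the number of days from visit 2 to 3 (or from 6 to 7). The part of the water-only week inside the change is min(g, 7) days. The 48 h exercise restriction lies wholly inside it whenever g is at least 2. Because g is not stated, I take a range.

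- *Diary reading (assumption).* Section 3.4 mentions a 10-day weighed food diary, and Table 2 ticks the diary at visits 2 to 5 and 6 to 9. If it spans visit 2 to visit 5, with about 3 fasting and 4 refeeding days, then g = 10 - 3 - 4 = 3 days. About 3 of the 7 water-only days fall in the change, and the other 4 precede the ECG.
- *Phase 2, water-only week after a full washout.* Visit 6 is at visit 4 + 28 days. Refeeding ends at visit 4 + 4, so four further weeks of usual lifestyle end at visit 4 + 32. A water-only week starting then puts visit 7 at visit 4 + 39 or later, so g is at least 39 - 28 = 11 days and the whole week is included.
- *Phase 2, water-only week overlapping the washout.* With visit 7 at visit 4 + 32, g = 32 - 28 = 4 days and 4 of the 7 days are included.

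In all three cases g is at least 2, so the 48 h restriction falls entirely after the ECG.

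**3. What the crossover removes**

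The run-in and the ECG schedule are the same in both periods. Write a participant's HRV change as (fast effect + r) under Intervention A and (fast effect + exercise effect + r) under Intervention B, where r is the run-in shift. The difference, B minus A, is the exercise effect and r drops out. The mean within-period change keeps r in full.

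**4. Illustration of size**

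Inputs: n = 20 completers, from section 5.5 (25 recruited, 20% dropout: 25 × 0.80 = 20); paired t-test, two-sided 0.05, 19 degrees of freedom; a true fasting effect of zero. The shift sizes are assumptions, since the documents give no HRV variance and no effect of caffeine or exercise on HRV.

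Rejection probability = P(|T| > 2.093), where T is noncentral t with noncentrality d√20 and d is the shift in SDs of the paired difference. If the shift is instead in within-person SDs with independent errors at the two visits, the SD of the difference is √2 times larger and d is the shift divided by √2.

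| Assumed shift | d if SD of paired difference | Rejection | d if within-person SD | Rejection |
|---|---|---|---|---|
| 0.2 | 0.20 | 13.6% | 0.14 | 9% |
| 0.3 | 0.30 | 24.7% | 0.21 | 15% |
| 0.5 | 0.50 | 56.5% | 0.35 | 32% |

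The nominal rate is 5%. At a shift of 0.1 SD of the paired difference the rate is 7.1%, so a small shift does little harm.

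**The case against.** The strongest reply has four parts.

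*The gap is unknown.* The article may simply leave the interval to the full protocol, and on the diary reading most of the water-only week is already past when the ECG is recorded. This stands as a limit on the claim. A reader might infer from Table 2 that the HRV change contains a full week of caffeine withdrawal and a week of exercise restriction. The documents support neither: the exercise restriction is 48 h and covers strenuous exercise only, and the share of the water-only week inside the change depends on the unstated gap. The objection does not remove the point, which rests on where the printed schedule puts the ECG and not on the missing interval.

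*The randomised comparison is protected.* This also stands. The primary hypothesis concerns Intervention B against Intervention A, and a common run-in shift cancels there. It would be wrong to read this point as a threat to that contrast or to the primary outcome.

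*The before-after change has no control in any case.* True: moving the ECG would not make it a controlled estimate. It would still remove one avoidable contaminant, and a baseline that was never recorded cannot be recovered in the analysis.

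*The direction and size of any run-in effect on HRV are not in the documents.* This stands too. The percentages are an illustration and depend on which SD the shift is measured in, so both scales are shown.

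**Conclusion.** The point holds in a limited form. The ECG baseline is earlier than the baselines for FMD and blood, and the within-period HRV change may include some or all of the water-only week. For any gap of 2 days or more it also includes the whole 48 h restriction on strenuous exercise. The consequence is confined to the uncontrolled before-after effect of fasting on HRV and heart age, a secondary outcome.

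Under assumed shifts of 0.2 to 0.5 SD, the chance of reporting a fasting effect that is not there runs from about 9% to 56%, depending on the shift and its scale. These figures assume 20 completers, a paired test and no true fasting effect. They show what is possible and do not estimate the bias.

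**What to change.** In Table 2, move the resting ECG from visits 2 and 6 to visits 3 and 7. Record it among the initial assessments that section 4.2 places before the exercise, or before the rest period under Intervention A, alongside FMD. State that this recording is the pre-fast baseline for HRV and heart age.

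The number of ECGs does not change. The cost is a few more minutes at visits 3 and 7 (3.5 h each), offset by fewer at visits 2 and 6 (2 h each). Section 3.5 discloses the allocation on arrival at visit 3, so the ECG would share that timing with FMD and blood unless it is recorded first. Keeping the recordings at visits 2 and 6 as well is optional; it would add two ECGs and show how far HRV moves over the run-in.

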### 3.7. Intervention

After completing the baseline assessments, participants will be randomly assigned to one of two groups: (1) Group 1 will undergo a prolonged water-only fast (Intervention A), while Group 2 will engage in a prolonged water-only fast accompanied by a single session of glycogen-lowering endurance exercise (Intervention B) during phase 1. Following this phase and a 4-week washout period, the groups will switch interventions in phase 2, with Group 1 undergoing Intervention B and Group 2 undergoing Intervention A. For a graphical representation of the experimental design, refer to Figure 1 and Figure 2.

**Table 3 nutrients-16-04297-t003:** Eligibility Criteria for the PROFASTA Trial.

Inclusion Criteria	Exclusion Criteria
• Healthy males and females without disabilities affecting cycling ability	• Pregnancy, breastfeeding, or unwillingness to use contraception if of childbearing potential
• Age 18–70 years	• History of chronic diseases affecting exercise capacity or result interpretation
• BMI 20–40 kg/m^2^	• Presence of comorbidities (hypertension, diabetes, cardiovascular disease)
• Ability to comply with all study procedures and assessments	• Current use of supplements or medications that may affect results
	• Health conditions, dietary requirements, or psychosocial factors affecting compliance
	• Unintentional weight loss >10% of body weight in past 5 years
	• Current smoking, psychiatric conditions, or history of substance abuse/eating disorders
	• Inability to complete baseline exercise tests (incremental peak power test or 90-min glycogen-depleting exercise)

Note: All criteria must be met for study participation. BMI, body mass index.

## 4. Fasting and Exercise Interventions

### 4.1. Three-Day Fasting Protocol

Participants will undergo a three-day (approximately 84 h, including 12 h overnight fasting before clinic visit) water-only fast at home, with remote monitoring and support from the study team. Throughout the fasting and refeeding phases, participants will report their wellbeing and symptoms via an online questionnaire and can contact study coordinators through email, SMS, or phone. Adherence will be monitored using a continuous glucose monitor (CGM) and by measuring morning and evening beta-hydroxybutyrate (BHB) ketone and glucose levels through fingerpick capillary blood. Participants will communicate their glucose and ketones readings to the trial coordinator, who will also review the data stored in the device during clinic visits. The CGM data will be streamed to an online dashboard monitored by research staff.

A week prior to the fasting intervention, participants will transition to consuming only water for hydration to reduce dependence on caffeine and caloric beverages. They will refrain from strenuous exercise for 48 h before the fasting assessment. On the day before fasting begins, participants will consume only water from 9 PM onward and record all food and drink intake in a diary for submission after the refeeding assessments. During fasting, participants are advised to drink 2–3 litres of water daily, with unflavoured carbonated and mineral water permitted. If participants find it too challenging to continue water-only fasting, they will be provided with 250 mL of vegetable broth sourced from Undivided Food Co., Sydney, Australia, which contains 110 kJ of energy, 0.8 g of protein, 0 g of fat, 5.8 g of carbohydrate and 375 mg of sodium per 250 mL serving. A maximum of two servings per day will be provided. Light physical activities such as walking, yoga, or stretching are encouraged, while strenuous exercise is not recommended. On the last fasting day, following clinic assessments, food will be gradually reintroduced, starting with vegetable broth and transitioning to a low-carbohydrate vegetarian diet. This initial diet will consist of small portions of non-starchy vegetables, salads, and soups for the first day, then gradually transitioning to their normal diet by the end of the refeeding period. This gradual reintroduction of food aims to minimise potential adverse effects and gastrointestinal symptoms. The vegetable broth will be offered upon completion of the fasting visit, along with instructions for the subsequent four days of the refeeding period. The rest of the meals of the refeeding period will not be provided; however, the participants will log all the food and drink into the food diary. Once the refeeding period concludes, participants will be instructed to resume their usual lifestyle for a 4-week washout period.

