## 2. Aims of Profasta Trial

The primary aim of the PROFASTA trial is to evaluate the impact of a three-day water-only fast, with and without a single session of glycogen-depleting exercise, on autophagic flux in isolated peripheral blood mononuclear cells (PBMCs) where flux is measured by the introduction of a lysosomal inhibitor into whole blood. The primary hypothesis is that glycogen depletion through exercise prior to fasting will significantly enhance autophagic activation in PBMCs. Secondary objectives include assessing changes in body composition, heart rate variability, endothelial function (measured via flow-mediated vasodilation), as well as plasma metabolomic and proteomic shifts, and microbiome metagenomic adaptations in stool samples.

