### 3.5. Randomisation

Participants will be randomly assigned using a web-based system in REDCap, employing random permuted blocks with a block size of four. Randomisation will occur at the beginning of visit 3, after all baseline measurements have been completed (Figure 1, Table 1). The study coordinator will disclose group assignments to both the study team and the participant upon their arrival for the clinic visit #3. While blinding participants and investigators is not feasible due to the nature of the intervention, those conducting sample analysis and statistical analysis will remain blinded to group allocations, when possible.

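### Food before each fast is recorded but not matched between periods: this adds within-person noise to starting glycogen and, because only the phase 2 intervention is known in advance, lets intake differ by intervention in phase 2

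*Protocol article*

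**What the plan says.** Section 4.1 of the protocol article sets out the preparation for a fast:

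- Drinks: "A week prior to the fasting intervention, participants will transition to consuming only water for hydration".
- Exercise: "They will refrain from strenuous exercise for 48 h before the fasting assessment".
- Overnight cut-off on the day before: "participants will consume only water from 9 PM onward".
- Food: participants are to "record all food and drink intake in a diary for submission after the refeeding assessments".

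No food is prescribed or provided before the fast, and there is no request to repeat the phase 1 intake in phase 2. After the first refeeding period, "participants will be instructed to resume their usual lifestyle for a 4-week washout period".

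On knowledge of allocation, section 3.5 says: "The study coordinator will disclose group assignments to both the study team and the participant upon their arrival for the clinic visit #3". It also states that participants cannot be blinded. Section 3.7 fixes what follows: "the groups will switch interventions in phase 2, with Group 1 undergoing Intervention B and Group 2 undergoing Intervention A".

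The primary hypothesis in section 2 is that "glycogen depletion through exercise prior to fasting will significantly enhance autophagic activation in PBMCs". Section 5.6 adjusts for usual diet as a baseline characteristic. It does not mention what was eaten before each fast.

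**The concern.** The contrast between interventions is about glycogen at the outset of the fast. Exercise is meant to lower it, and food eaten in the preceding day or days acts on the same store. The preparation rules control three influences and leave food free until the evening cut-off. No procedure in Table 2 and no outcome in sections 5.1 to 5.3 measures glycogen, so a difference in starting level between a participant's two periods would not be seen directly.

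Two things are at stake. The first is precision: a crossover gains its efficiency from comparing a person with themselves, and unmatched intake adds to the within-person variation that this comparison is judged against. The second is a possible systematic difference. In phase 2 a Group 1 participant knows that fasted cycling is coming and a Group 2 participant knows that rest is coming. Section 4.2 describes 60 minutes of steady cycling followed by up to ten sprints, with withdrawal from that arm for those who fall short of a stated minimum. That is an understandable reason to eat differently beforehand. Any such response would line up with B versus A, and randomisation does not remove it because it arises after disclosure.

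**Working it through.** The point rests on no figure in the plan, so there is no figure to reproduce. The check is a comparison of what is known when, followed by short algebra.

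**Timing (Table 1, sections 3.5, 3.7 and 4.1)**

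| | Phase 1 | Phase 2 |
|---|---|---|
| Pre-fast eating ends | 9 PM before visit 3 | 9 PM before visit 7 |
| Intervention becomes known | on arrival at visit 3 | already fixed at visit 3 |
| Can pre-fast eating depend on the intervention? | no | yes |

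**Notation.** Let c(i,j) be pre-fast intake of participant i in phase j, and b the effect of a unit of that intake on flux. That b differs from zero is in the spirit of the trial's own hypothesis, but the document does not show it. Let T be the true B-minus-A effect and P the phase effect (phase 2 minus phase 1). Group 1 receives A then B; Group 2 receives B then A.

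**Noise.** A participant's B-minus-A difference contains b × (intake before B − intake before A). With unmatched intake, this adds b² × Var(intake before B − intake before A) to the variance of the within-person difference. A habitual-diet covariate takes the same value in both periods, so as a main effect it cancels from the difference and removes none of this.

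**Systematic part.** Write m(g,j) for mean intake in group g before the phase j fast. The mean B-minus-A differences are:

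- Group 1: T + P + b × [m(1,2) − m(1,1)]
- Group 2: T − P + b × [m(2,1) − m(2,2)]

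The crossover estimate is their average:

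T + (b/2) × {[m(1,2) − m(2,2)] − [m(1,1) − m(2,1)]}

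The second bracket compares the groups before allocation was known, so its expectation is zero. That leaves g/2, where g = b × [m(1,2) − m(2,2)] is the shift in flux caused by the groups eating differently before the phase 2 fast.

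**Two consequences.** A change in eating shared by both groups in phase 2, for instance because both have fasted once already, cancels. Only a difference between the groups counts, and half of it reaches the estimate. Neither b nor m(1,2) − m(2,2) can be obtained from the document, so g has no derivable size or sign.

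**The case against.** The best answer to this point has five parts.

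- **Condensed article.** The full protocol or participant instructions may ask for a repeated diet, and section 3.4 says that a registered dietitian and study personnel instruct participants. This is possible. But section 4.1 describes the preparation closely, down to the composition of the broth, and for pre-fast food it states recording only. The point therefore concerns a conduct choice as written, more than a missing detail.
- **Existing controls.** A week with water as the only drink removes caloric beverages, and 48 hours without strenuous exercise limits another influence on glycogen. This stands, and it narrows the problem to food. Table 2 also schedules fasting blood and capillary glucose and ketones at visits 3 and 7, and section 4.2 places the exercise after the initial assessments. A baseline for each period is therefore available, although it does not show glycogen.
- **Common motive.** Both groups face the same fast of about 84 hours, which may change eating more than the exercise does. This stands too: a shared change cancels.
- **No evidence of differential eating.** A reader might infer that participants will eat more carbohydrate before the exercise and that the trial is therefore biased towards no effect. The documents do not support this. They show that the phase 2 intervention is known, not that anyone eats differently, in which direction, or that flux responds.
- **Analysis detail.** A sensitivity model is normally left to the analysis plan, and phase 2 intake may itself follow allocation, so adjusting for it is not a clean correction. This stands and shapes the fix.

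**Conclusion.** The point holds as a weakness of conduct. Pre-fast food is uncontrolled between periods in a trial whose primary contrast concerns glycogen, and the planned diet covariate cannot repair a within-person difference. The certain part is modest: to the extent that intake varies between a person's periods and affects flux, it adds within-person noise. The conditional part is that intake can differ by intervention in phase 2 but not in phase 1, and that half of any resulting shift in flux would enter the B-minus-A estimate. This rests on two assumptions that the document does not settle: that participants respond to the known intervention in what they eat, and that this intake affects flux.

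No numerical bias or loss of precision should be attached to it. Section 5.5 gives a single standard deviation without saying whether it is within or between persons, and nothing in the document gives a diet effect or a share of variance due to diet. A reader might want to go further and call the primary comparison biased, but that is not shown. The reason to act is that matching is cheap beforehand, whereas a mismatch can be repaired only in part afterwards.

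**What to change.** In section 4.1, add that each participant receives a copy of their own phase 1 diary for the pre-fast day or days by visit 6, early enough to cover the corresponding days before visit 7, and is asked to repeat that intake. The phase 1 diary is due after the refeeding assessments (visit 5), so it is in hand before it is needed.

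Report diary carbohydrate intake before each fast by intervention and phase, descriptively. This shows whether matching worked and whether phase 2 intake followed the intervention. Any model that adjusts for this intake should be labelled exploratory, because in phase 2 the covariate may itself be a consequence of known allocation. It should not replace the primary analysis.

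The cost is a copy of a document already collected, one instruction and one descriptive table. The downsides are a slight burden on participants and imperfect compliance, so matching will reduce the difference between periods without removing it. Randomisation, visits, interventions and sample size are unaffected. If the full protocol already contains such an instruction, a sentence in section 4.1 saying so is enough.
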